# Implications

The results can:

1. provide empirical data on the QOC of PEP provided by the contractor (NGO) of HA;
2. provide evidence on whether the PEP can enhance patients on self-efficacy and knowledge of their diseases;
3. provide information on the effectiveness of PEP in improving the outcome of care for DM and HT patients, in order to guide policy decision making.

# Compliance with the ICH-GCP

This protocol is complied with the ICH-GCP.

## Appendix B: Structure of care questionnaire

| **PEP Structure of Care Questionnaire** | | | |
| --- | --- | --- | --- |
| **Please indicate whether the following statement is applicable for your clinic.** | | | |
|  | | | |
| 1 | There **must** be at least 1 registered nurse, 1 healthcare professional and 1 clerical staff in the participating NGO. | Yes | No |
|  |  |  |  |
| 2 | The in-charge staff in each NGO **should** be familiar with the programme objectives and logistics. | Yes | No |
|  |  |  |  |
| 3 | The in-charge staff in NGO **should** know the recruitment, enrolment and programme protocol. | Yes | No |
|  |  |  |  |
| 4 | The in-charge staff in Cluster Programme Office **should** have undergone PPi-PEP and e-Referral training for this programme. | Yes | No |
|  |  |  |  |
| 5 | Specific data collection forms (electronic) **must** be used to collect patient data for this programme. | Yes | No |
|
|  |  |  |  |
| 6 | Clinical staff **must** have access to the e-referral system for patient referral. | Yes | No |
|
|  |  |  |  |
| 7 | NGO staff **should** have access to the PPI-PEP system for patient data collection and retrieval. | Yes | No |
|  |  |  |  |
| 8 | Facilities for patient recruitment and enrollment **should** be available in the clinic. | Yes | No |
|  |  |  |  |
| 9 | Toolkits on generic self-efficacy enhancement and lifestyle modification component **should** be available | Yes | No |
|
|  |  |  |  |
| 10 | Toolkits on specific disease knowledge on DM and HT **should** be available in NGO | Yes | No |
|  |  |  |  |
| 11 | There **must** be a record of patients referred in the PPI-PEP system shared by authorized members of the programme. | Yes | No |
|  |  |  |  |
| 12 | There **should** be a record of enrolled patients in the PPI-PEP system shared by authorized members of the programme. | Yes | No |
|  |  |  |  |
| 13 | The patients’ doctor **should** be able to access the information that the patient has enrolled to the PEP. | Yes | No |
|  |  |  |  |
| 14 | After completion of the programme, the end-of-programme summary **could** be available for the patient to their doctors. | Yes | No |
|  |  |  |  |
| 15 | There **should** be meetings among staff of the participating NGO to monitor the performance of the programme. | Yes | No |

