## Hypotheses

The following hypotheses will be tested:

1. The criteria on structure and process should be achieved by all participating clinics and NGO;
2. More patients with DM will achieve the target HbA1c after 12, 24, 36 and 48 months in the PEP programme;
3. More patients with HT or DM will achieve the target blood pressure levels after 12, 24, 36 and 48 months in the PEP programme;
4. In longer terms, HT/ DM patients will have reduced cardiovascular risks and fewer complications;
5. Patients should report an improvement in quality of life (QOL), enablement and overall health condition after the PEP programme;
6. Patients who take part in PEP programme should not have any increase in service utilization rates.

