## Data Collection

Evaluation on structure and process

The co-ordinator of each participating clinic and all participating NGO will be asked to complete the structure of care questionnaire (appendix B). Anonymized data will be retrieved from the computerized medical record system (CMS) by the HA Statistics team to determine the patient recruitment rate, enrollment rate, attendance rate, compliance with assessment as per protocol, number of investigations and referral rate.

Evaluation on outcomes of care

Anonymized data on HbA1c, blood pressure (BP), low-density lipoprotein (LDL), body mass index (BMI) and annual attendance rates for GOPC, specialist outpatient clinic (SOPC) , accident and emergency (A&E) and hospital attendance rates, patient knowledge on disease at baseline and 12 months will be retrieved from the CMS by the HA Statistics team. The audit cycle will be repeated annually over a period of 5 years. This data will be extracted are shown in the data collection form in appendix C.

The 550 patients in the PEP programme who are willing to take part in the telephone survey will be contacted by a trained research assistant who will obtain verbal consent from each patient. Each patient will then answer the Chinese (Hong Kong) Short Form-12 version 2 (SF-12v2) Health Survey within one month from enrolment, and then at 6, 12, 36 and 60 months to repeat the SF-12v2 together with the Patient Enablement Instrument (PEI), Global Rating Scale (GRS) of change in health condition and private service utilization (appendix D).

- 1. The Chinese (Hong Kong) Short Form-12 version 2 (SF-12v2) Health Survey is a generic measure HR QOL. It has been validated and normed on the general Chinese population in Hong Kong (Lam, Wong et al. 2010). It measures eight domains on physical functioning, role physical, bodily pain, general health, vitality, social functioning, role emotional and mental health on a scale range from 0 to 100. A higher score indicates better HRQOL. The eight domain scores can be summarized into two summary scores, the physical (PCS) and mental (MCS) component summary.

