## Outcome measures

**Primary**

- The proportion of clinics/NGO that have satisfied each of the set structure criteria.
- The proportion of patients who have complied with the criterion process of care.
- The proportion of DM patients who have achieved a HbA1c level <7%.
- The proportion of HT/ DM patients who have achieved the target blood pressure.
- The estimated 10-year cardiovascular disease risk.

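### The structure questionnaire (Appendix B) does not reliably show whether criteria are met: it asks if requirements are applicable, and clinics must answer Yes or No on items about other bodies

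*Protocol*

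**What the plan says.** Hypothesis 1 of the protocol reads "The criteria on structure and process should be achieved by all participating clinics and NGO". The first bullet under Outcome measures, Primary, is the matching endpoint: "The proportion of clinics/NGO that have satisfied each of the set structure criteria". Item 1 of Data analysis plans a descriptive percentage of centres for each structure criterion.

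Data Collection names one source for structure data: "The co-ordinator of each participating clinic and all participating NGO will be asked to complete the structure of care questionnaire". The record-system extract described next to it covers recruitment, attendance and other process data, not structure.

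The form is Appendix B. Its stem is "Please indicate whether the following statement is applicable for your clinic". Fifteen statements follow, each built on must, should or (item 14) could, with Yes and No as the only answers. Item 1 is an example about the NGO: "There must be at least 1 registered nurse, 1 healthcare professional and 1 clerical staff in the participating NGO". Item 4 is about a third body: "The in-charge staff in Cluster Programme Office should have undergone PPi-PEP and e-Referral training for this programme". Nothing in the protocol says which respondent answers which item, or how to count an item that does not concern the respondent.

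**The concern.** The endpoint needs a fact about each organisation: is the criterion met or not? The form departs from this in two ways.

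- **Stem and wording.** It asks whether a statement of requirement is applicable. Read literally, a Yes to item 1 confirms that the staffing rule applies, not that the staff are in post. The choice of reading is left to each co-ordinator.
- **Respondent.** A clinic co-ordinator is asked about the NGO's staffing, training and meetings, and about the cluster office's training, with no way to say that the item is not theirs or that they do not know. The phrase about the respondent's own clinic also does not fit an NGO.

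At stake is a listed primary outcome whose target is full compliance. With that target, even a few misdirected No answers would appear to contradict Hypothesis 1. The structure results are also part of what is fed back to the programme team to decide on quality enhancement.

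**Working it through.** The plan states no figure for this point, so there is nothing to reproduce. The check compares the form with the endpoint, counts items by the body they describe, and then bounds the possible effect.

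**Step 1: items by body described (Appendix B).**

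| Body | Items | Count |
| --- | --- | --- |
| NGO, named | 1, 2, 3, 7, 10, 15 | 6 |
| Cluster Programme Office, named | 4 | 1 |
| Clinic side (item 8 names the clinic; 6, 13 and 14 concern clinical staff or the patient's doctor) | 6, 8, 13, 14 | 4 |
| No body named | 5, 9, 11, 12 | 4 |

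For a clinic respondent, 6 + 1 = 7 of 15 items (47%) concern another body. For an NGO respondent, the six NGO items are its own. Item 4 belongs to neither type of respondent.

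**Step 2: what an answer can mean.** On the seven items, a clinic's No may mean that the criterion is unmet, that the item is not the clinic's, or that the co-ordinator does not know. The form records all three identically. On any item, a Yes means met if the stem is taken as *true of us*, but only that the rule applies if it is taken literally.

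**Step 3: possible size.** The protocol gives no number of clinics or NGOs and does not say whether their answers are pooled, so everything here is an assumption. Take one NGO item that every NGO meets and reports as met. Let *c* be the clinics' share of respondents and *f* the fraction of clinics that tick No because the item is not theirs or not known to them; the other clinics tick Yes. If all answers are pooled:

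reported proportion = (1 − c) + c(1 − f) = 1 − c × f

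| c | f = 0 | f = 0.5 | f = 1 |
| --- | --- | --- | --- |
| 50% | 100% | 1 − 0.5 × 0.5 = 75% | 1 − 0.5 = 50% |
| 80% | 100% | 1 − 0.8 × 0.5 = 60% | 1 − 0.8 = 20% |
| 90% | 100% | 1 − 0.9 × 0.5 = 55% | 1 − 0.9 = 10% |

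The true value is 100% in every cell. If NGO answers are tabulated alone, the reported value is also 100%, and the problem for that item disappears.

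**The case against.** The strongest reply is that the intent is plain. Most co-ordinators in a quality audit would take the stem to ask whether the statement is true of their organisation, and the endpoint and Data analysis wording point the same way. Must, should and could may only grade how binding each criterion is, so the wording of item 14 is weak evidence of a flaw. NGOs receive the form too and can answer the six NGO items properly. An analysis plan, which is not shown, could set item-specific denominators.

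Importance can also be questioned. The analysis is descriptive and touches no comparison between participants and controls. The abstract does not list structure among its primary outcomes. The Methods describe iterative development of the framework, and the timeline puts its refinement (July to September 2010) before structure data collection (October 2010 to January 2011), so the form may not be final.

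Most of this stands and limits the point. It does not remove it. An analysis plan can choose a denominator, but it cannot recover what a No meant or add an answer that was never offered, and it cannot supply a proper respondent for item 4. The routing problem remains even on the favourable reading of the stem. Possible later refinement does not alter the form as this protocol sets it out.

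**Conclusion.** The concern holds in a limited form. As written, Appendix B does not reliably measure whether structure criteria are met. Clinic answers to items 1, 2, 3, 7, 10 and 15, and all answers to item 4, cannot be read as attainment. NGO answers to the six NGO items can be used if they are reported by respondent type.

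Three stronger conclusions are tempting but unsupported:

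- A reader might infer that the form does not measure attainment at all. The natural reading of the stem, given the endpoint, is that the statement is true of the respondent, and 7 of 15 items, not all, are misdirected for clinics.
- A reader might infer that one NGO's staffing is counted again by every clinic it serves. That requires pooling of clinic and NGO answers, which the protocol nowhere states.
- A reader might want a single figure for the distortion. Without the numbers of clinics and NGOs there is none. Under pooling, with clinics at 50% to 90% of respondents, the reported proportion for an item met by every NGO runs from 100% (no clinic ticks No) down to 50% to 10% (all do).

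This is a cheap and specific improvement to a descriptive primary outcome. It does not threaten the between-group results.

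**What to change.** In Appendix B:

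- Replace the stem with *Is this criterion currently met?* and word each item as a fact, for instance *The NGO has the required nursing, professional and clerical staff in post*. If must, should and could are meant as grades, show the grade in a separate column.
- Mark each item as answered by the clinic, the NGO or the cluster office. Add the cluster office as a respondent for item 4 in Data Collection.
- Offer *not applicable* and *do not know* beside Yes and No.

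Report each structure proportion among the organisations to which that item is addressed. This can be stated with the primary outcome or in the analysis plan.

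The work is the rewording of a short form. The downside is limited comparability with any answers already collected on the present form. For those, reporting by respondent type and leaving clinic answers to the seven items out of the attainment figures rescues the six NGO items but not item 4.

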## Appendix C: Data collection form for extraction of data from the HA medical records

| **Data Required** | **Number of  patients** | **Time (in days) from recruitment** |
| --- | --- | --- |
|
| Uptake of programme* | | |
| Patients identified eligible |  | NA |
| Patients recruited |  | NA |
| Patients enrolled |  |  |
| Process of care* | | |
| Patients attended at least 1 generic session |  |  |
| Patients attended at least 1 disease specific session |  |  |
| Patients completed the programme |  |  |
| Patients dropped out or discharged from programme |  |  |
| Patients identified to have problems (e.g. poor drug compliance, overweight, foot deformity, smoking) |  |  |

*include only subjects who have enrolled more than 12 months

**Patients require special treatment:**

| **Data Required** | **Number of  patients** | **Time (in days) from problem recognition** |
| --- | --- | --- |
|
| Identified to have problem being given treatments per protocol |  |  |
| Referred for additional service |  |  |
| Refused additional service |  |  |

| **Time (Month)** | **Data required** |
| --- | --- |
| 0, 12, 24, 36 and 48 | **Clinical data** |
| HbA1c |
| Systolic BP |
| Diastolic BP |
| BMI |
| LDL-C |
| **Service utilization** (in the past 12 months) |
| Number of hospitalization |
| Number of A&E attendance |
| Number of GOPC consultation |
| Number of SOPC consultation |
| 0 and 6 months | **Patient reported** |
| Disease knowledge score |
| QoL score |
| PEI* |
| GRS* |

BP = Blood Pressure; BMI = Body Mass Index; LDL-C = Low density Lipoprotein Cholesterol; GOPC = General Outpatient Clinic; SOPC = Specialist Outpatient Clinic; KAP = Knowledge, Attitude and Practice.

*Measured at 6 months only.

**標準十二題簡明健康狀況調查表-第**二**版**

**說明：這項調查是詢問您對自己健康狀況的了解。此項資料記錄您的自我感覺和日常生活的情況。**

**請在一個方格內填上X號來回答每個問題。如果您不肯定怎樣回答，請按照您的理解選擇最合適的答案。**

**1. 總括來說，您認為您的健康狀況是：**

| 極好 | | 很好 | | 好 | | 一般 | | 差 |
| --- | --- | --- | --- | --- | --- | --- | --- | --- |
| 1 | 2 | | 3 | | 4 | | 5 | |

**2. 下列問題是您日常生活中可能進行的活動。以您目前的健康狀況，您在進行這些活動時，有沒有受到限制？如果有的話，程度如何？**

|  | 有很大限制 | 有一點限制 | 沒有任何限制 |
| --- | --- | --- | --- |
| a. 中等強度的活動，比如搬桌子，使用吸塵器清潔地面，玩保齡球或打太極拳 | 1 | 2 | 3 |
| b. 上幾層樓梯 | 1 | 2 | 3 |

**3. 在過去四個星期裏，您在工作或其它日常活動中，有多少時間會因為身體健康的原因而遇到下列的問題？**

|  | 常常如此 | 大部分時間 | 有時 | 偶爾 | 從來沒有 |
| --- | --- | --- | --- | --- | --- |
| a. 實際做完的比想做的要少 | 1 | 2 | 3 | 4 | 5 |
| b. 工作或其它活動的種類受到限制 | 1 | 2 | 3 | 4 | 5 |

**4. 在過去的四個星期裏，您在工作或其它日常活動中，有多少時間由於情緒方面的原因（比如感到沮喪或焦慮）遇到下列的問題？**

|  | 常常如此 | 大部分時間 | 有時 | 偶爾 | 從來沒有 |
| --- | --- | --- | --- | --- | --- |
| a. 實際做完的比想做的要少 | 1 | 2 | 3 | 4 | 5 |
| b. 工作時或從事其它活動時不如往常細心了 | 1 | 2 | 3 | 4 | 5 |

**5. 在過去四個星期裏，您身體上的疼痛對您的日常工作（包括上班和家務）有多大影響？**

| 毫無影響 | | 有很少影響 | 有一些影響 | | 有較大影響 | | 有極大影響 |
| --- | --- | --- | --- | --- | --- | --- | --- |
| 1 | 2 | | 3 | 4 | | 5 | |

**6. 下列問題是有關您在過去四個星期裏您覺得怎樣和您其它的情況。針對每一個問題，請選擇一個最接近您的感覺的答案。在過去四個星期裏有多少時間：**

|  | 常常如此 | 大部分時間 | 有時 | 偶爾 | 從來沒有 |
| --- | --- | --- | --- | --- | --- |
| a. 您感到心平氣和？ | 1 | 2 | 3 | 4 | 5 |
| b. 您感到精力充足？ | 1 | 2 | 3 | 4 | 5 |
| c. 您覺得心情不好，悶悶不樂？ | 1 | 2 | 3 | 4 | 5 |

**7. 在過去四個星期裏，有多少時間由於您的身體健康或情緒問題妨礙了您的社交活動 (比如探親、訪友等）？**

| 常常有妨礙 | | 大部分時間有妨礙 | | 有時有妨礙 | | 偶爾有妨礙 | | 完全沒有妨礙 |
| --- | --- | --- | --- | --- | --- | --- | --- | --- |
| 1 | 2 | | 3 | | 4 | | 5 | |

多謝您參與研究！

----------------------------------------------------完-------------------------------------------------

**私家醫療服務的使用**

| 1. **在過去四個星期裏，**你有冇睇過私家醫生 (西醫 / 中醫)？  *(如答沒有, 回答問題2)* | 1.  2. | | | 有  沒有 | | | | | | | | | |
| --- | --- | --- | --- | --- | --- | --- | --- | --- | --- | --- | --- | --- | --- |
|  | 1. | 普通科 | | | | 2. | 專科 | | | 3. | 中醫 | | |
| a. 請問你睇過私家醫生幾多次？ | 1. | | | | 次 | 2. | 次 | | | 3. | 次 | | |
| b. 請問你由屋企**平均**要搭幾耐車先到私家診所呢？ | 1. | | | | 分鐘/小時 | 2. | 分鐘/小時 | | | 3. | 分鐘/小時 | | |
| c. 請問你由屋企搭車去私家診所要幾多錢呢？ | 1. | | | |  | 2. |  | | | 3. |  | | |
| d. 請問你睇一次私家醫生**平均**要幾耐？ (包括等候同埋見醫生嘅時間) | 1. | | | | 分鐘/小時 | 2. | 分鐘/小時 | | | 3. | 分鐘/小時 | | |
| e. **每次**求診嘅費用有幾多  (包括僱主或保險公司嘅補貼)？ | 1. | | | |  | 2. |  | | | 3. |  | | |
| f. 有冇人陪你睇私家醫生呢？佢係邊個？  (性別：男/女) | 1. | | i.  ii. | | 有 ( 男/女 )  沒有 | 2. | | i.  ii. | 有 ( 男/女 )  沒有 | 3. | | i.  ii. | 有 ( 男/女 )  沒有 |
| g. 佢有冇請假呢？ | 1. | | i.  ii. | | 有  沒有 | 2. | | i.  ii. | 有  沒有 | 3. | | i.  ii. | 有  沒有 |

| 2. **在過去四個星期裏，**你有冇試過自己買藥食？  *(如答沒有, 回答問題3)* | 1.  2. | 有  沒有 | |
| --- | --- | --- | --- |
| 怎樣處理，幾多次，**每次**幾多錢？ | 次數 | | 每次費用 ($) |
| 1. 西藥成藥 | 1. | | 2. |
| b. 中藥成藥 (例如：牛黃解毒片、銀翹) | 1. | | 2. |
| c. 中草藥 (藥材舖執藥) | 1. | | 2. |
| 1. 其他，請註明：______________ | 1. | | 2. |

| 3. **在過去六個月裏，**你有冇入住私家醫院？  *(如答沒有, 回答問題4)* | 1.  2. | 有  沒有 |
| --- | --- | --- |
| a. 請問你留左幾多日院呢？ | 日 | |
| b. 請問你由屋企**平均**要搭幾耐車先到私家醫院呢？ | 分鐘/小時 | |
| c. 請問你由屋企搭車去私家醫院要幾多錢呢？ | $ | |
| d. **上一次**入住醫院嘅費用有幾多  (包括僱主或保險公司嘅補貼)？ | $ | |
| e. 有冇人係你**上一次**入院時照顧患病嘅你？佢係邊個？ (性別：男/女) | 1.  2. | 有 _____ (男/女)  沒有 |
| f. 係你**上一次**入院時佢請咗幾多日假照顧你？ | 日 | |

**家居照顧**

| 4. **在過去六個月裏，**當你患病嘅時候有冇人照顧你嘅起居飲食？佢係邊個？ (性別：男/女) | 1.  2. | 有 _____ (男/女)  沒有 | | |
| --- | --- | --- | --- | --- |
| 4a. 佢洗唔洗請假照顧你？唔番工定係唔番學？如果要請假，請幾多日呢？ | 1. | 有 | i.  ii. | 唔番工________日  唔番學 ________日 |
| 2. | 沒有 | | |

**生活方式**

吸煙

| 5. 你有冇食煙嘅習慣？*(如答沒有, 回答問題****5e****)* | 1.  2. | | 有  沒有 | | | | |
| --- | --- | --- | --- | --- | --- | --- | --- |
| a. 請問你食煙嘅習慣是： | 1. 現在完全戒煙 | | | | | 2. 現在間中食煙，每日不夠一支 | 3. 現在每日食煙起碼一支 |
| b. 請問你已戒煙有幾耐？ | ___年___ 月 | | | | |  |  |
| c. 請問你(以前 / 現在)平均每日吸多少支煙? | 1. 支 | | | | | 2. 支 | 3. 支 |
| d. 請問你食左幾多年煙？ | 1. 年 | | | | | 2. 年 | 3. 年 |
| e. 不計算你自己，請問你**屋企**同埋**工作範圍**有沒有其他人食煙呢？ | 1. | 屋企: | | i.  ii. | 有  沒有 | | |
| 2. | 工作範圍: | | i.  ii. | 有  沒有 | | |

運動習慣

| 6. 你有冇定期做運動嘅習慣？  *(如答沒有, 回答問題7)* | 1.  2. | 有  沒有 | | | | |
| --- | --- | --- | --- | --- | --- | --- |
| a. 你是參與什麼類型的體育活動(你可選擇多過一個答案) | 1.有氧健身法 | | 2. 舒展運動 | 3. 平路慢步 | 4. 太極/瑜珈 | 5. 其他： _________ |
| b. 每星期做幾多次運動？ | 1. ____ 次 | | 2. _____ 次 | 3._____ 次 | 4._____ 次 | 5. _____ 次 |
| c. 你每次平均做幾耐運動？ | 1._____分鐘  a. < 15 分鐘  b. 15-30分鐘  c. > 30分鐘 | | 2._____分鐘  a. < 15 分鐘  b. 15-30分鐘  c. > 30分鐘 | 3._____分鐘  a. < 15 分鐘  b. 15-30分鐘  c. > 30分鐘 | 4._____分鐘  a. < 15 分鐘  b. 15-30分鐘  c. > 30分鐘 | 5.____分鐘  a. < 15 分鐘  b. 15-30分鐘  c. > 30分鐘 |

**個人資料**

| 7. 請問你嘅婚姻狀況係？ | 1. 單身 | | 2. 已結婚 | | | 3. 分居/離婚 | | | 4. 配偶去世 | | | | | 5. 拒絕回答 | | |
| --- | --- | --- | --- | --- | --- | --- | --- | --- | --- | --- | --- | --- | --- | --- | --- | --- |
|  |  | |  | | |  | | |  | | | |  | | | |
| 8. 請問你平均每月嘅家庭收入係 (包括所有來源)？  $________________ | 1.  少過  $2,000 | 2.  $2,000至$3,999 | | 3.  $4,000至$5,999 | 4.  $6,000至$7,999 | | | 5.  $8,000至$9,999 | | | 6.  $10,000至$14,999 | 7.  $15,000至  $19,999 | | | | 8.  $20,000至$24,999 |
| 9.  $25,000至$29,999 | 10.  $30,000至$39,999 | | 11.  $40,000至$59,999 | 12.  $60,000或  以上 | | | 13.  沒有收入 | | | 14.  拒絕  回答 | 15.  不知道 | | | |  |
|  |  | |  | | |  | | |  | | | |  | | | |
| 9. 請問你平均每月嘅個人收入係 (包括所有來源)？  $________________ | 1. 少過 $2,000 | | 1. $2,001   至  $5,000 | | | | 1. $5,001   至  $9,999 | | | 1. $10,000至$14,999 | | | | | 1. $15,000   至  $19,999 | |
| 1. $20,000 至$29,999 | | 1. $30,000或以上 | | | | 1. 沒有收入 | | | 1. 拒絕回答 | | | | | 1. 不知道 | |

----------------------------------------------------完----------------------------------------------------

**SF-12 HEALTH SURVEY (VERSION 2.0)**

INSTRUCTIONS: This survey asks for your views about your health. This information will help keep track of how you feel and how well you are able to do your usual activities.

Answer every question by marking the answer as indicated. If you are unsure about how to answer a question, please give the best answer you can.

1. In general, would you say your health is:

| Excellent | Very good | Good | Fair | Poor |
| --- | --- | --- | --- | --- |
| 1 | 2 | 3 | 4 | 5 |

2. The following questions are about activities you might do during a typical day. Does **your health now limit you** in these activities? If so, how much?

|  | Yes, limited a lot | Yes, limited a little | No, not limited at all |
| --- | --- | --- | --- |
| a. **Moderate activities**, such as moving a table, pushing a vacuum cleaner, bowling, or playing golf | 1 | 2 | 3 |
| b. Climbing **several** flights of stairs | 1 | 2 | 3 |

3. During the **past 4 weeks**, how much of the time have you had any of the following problems with your work or other regular daily activities **as a result of your physical health**?

|  | All of the time | Most of the time | Some of the time | A little of the time | None of the time |
| --- | --- | --- | --- | --- | --- |
| a. **Accomplished less** than you would like | 1 | 2 | 3 | 4 | 5 |
| b. Were limited in the **kind** of work or other activities | 1 | 2 | 3 | 4 | 5 |

4. During the **past 4 weeks**, how much of the time have you had any of the following problems with your work or other regular daily activities **as a result of any emotional problems** (such as feeling depressed or anxious)?

|  | All of the time | Most of the time | Some of the time | A little of the time | None of the time |
| --- | --- | --- | --- | --- | --- |
| a. **Accomplished less** than you would like | 1 | 2 | 3 | 4 | 5 |
| b. Did work or other activities less **carefully** than usual | 1 | 2 | 3 | 4 | 5 |

5. During the **past 4 weeks**, how much did **pain** interfere with your normal work (including both work outside the home and housework)?

| Not at all | A little bit | Moderately | Quite a bit | Extremely |
| --- | --- | --- | --- | --- |
| 1 | 2 | 3 | 4 | 5 |

6. These questions are about how you feel and how things have been with you during the **past 4 weeks**. For each question, please give the one answer that comes closest to the way you have been feeling. How much of the time during the **past 4 weeks**...

|  | All of the time | Most of the time | Some of the time | A little of the time | None of the time |
| --- | --- | --- | --- | --- | --- |
| a. Have you felt calm and peaceful? | 1 | 2 | 3 | 4 | 5 |
| b. Did you have a lot of energy? | 1 | 2 | 3 | 4 | 5 |
| c. Have you felt downhearted and depressed? | 1 | 2 | 3 | 4 | 5 |

7.During the **past 4 weeks**, how much of the time has your **physical health** or **emotional problems** interfered with your social activities (like visiting friends, relatives, etc.)?

| All of the time | Most of the time | Some of the time | A little of the time | None of the time |
| --- | --- | --- | --- | --- |
| 1 | 2 | 3 | 4 | 5 |

-------------------------------------------------end-----------------------------------------------

